# Procedures for Study Participation and Registration of Subjects

## Procedures for Research Participation

When participating in this study, the principal investigator at each study site shall affiliate with the "Agreement on the Clinical Study Protocol" and enter the necessary information such as the name of the study site and submit it to the Research Secretariat. The participation in each subcohort study (16. Conduct of subcohort study) should also be specified (participation in subcohort study is optional).16

After deciding to participate in this study, the ethics review committee will be requested to review the clinical study protocol, the clinical study protocol (Appendix version) of the participating subcohort study, and the informed consent form including the content of the subcohort study, and obtain approval.

## Contract Procedure

After approval by the Ethics Review Committee at each study site, a contract will be concluded between the CRO, which entrusts research activities, and each study site.

## Registration of study subjects

Registration of the study subjects will be performed on the EDC system of this study. The investigator or sub-investigator will obtain written informed consent from NVAF patient who may be eligible for the study, promptly access the registration system, and enter all of the following information:
　　・ Sex
　　・ Date of birth or age at the time of obtaining informed consent
　　・ Date of consent

The registered information will be promptly issued from the system, only if the eligibility criteria for this study are met (details will be in accordance with the EDC System Procedures).

# Methodologies

1. Application for Account to EDC System

The investigator will appoint a Research Doctor and Research Coordinator (e.g., Clinical Research Coordinator) and submit an application for an EDC system account for the study after the contract is concluded. After issuing accounts and passwords, the Study Doctor and Research Collaborator will log in to the EDC system and set the user name. Investigators and research collaborators should, as far as possible, be trained in operating procedures prior to the start of the study.

1. Written informed consent obtained from patients, etc.

During the conduct of this study, investigators and others will inform patients of patients who meet eligibility criteria using informed consent forms according to the present study and the sub-cohort study of the study in which they participate, and obtain written informed consent. If the patient is incapacitated, the consent of the legally acceptable representative is acceptable (see "7. Informed Consent" for details).7

1. Registration of study subjects

After obtaining written informed consent from the patients eligible for the study, the case registration system will be used to promptly enroll the patients. At the same time, investigators and others will create a corresponding table "Patient Identification Number Management Table" for patient chart number and patient registration number for the purpose of anonymisation of patient data in a linkable fashion so that individuals cannot be identified. In addition, strictly store it in a locked place within the study site.

1. Investigation of Observations

This study creates a form on the EDC system that enters survey information on the following observations:

- Baseline Survey: Data on the subject's background at entry (hereinafter, at baseline) (most recent data within 180 days of the date of informed consent)
- 12-Month Survey: The most recent data at 12 months after the date of informed consent (the most recent data at 12 months after baseline is preferred (tolerance: 1 year after the date of informed consent ± 60 days))
- 24-Month Survey: Most recent data at 24 months after the date of informed consent (most recent data at 24 months after baseline is preferred (tolerance: 2 years after the date of informed consent ± 60 days))

Investigators and research collaborators shall enter the data into the EDC system at each of the above time points for all registered research subjects and submit (transmit) the eCRF by electronic signature of the investigators etc. For data obtained in writing, such as output data from electronic medical records, patient questionnaires, etc. in subcohort studies, the Study Secretariat will register the data in the database.

1. Confirmation of health (including confirmation of occurrence of events and adverse events)

The investigator or sub-investigator will confirm the patient's well-being and the occurrence of events or adverse events as far as possible at 12 and 24 months after enrollment. Study subjects who do not have visits will be contacted by telephone, letter, or other means to search for event and adverse event information whenever possible. In addition, when transferring the patient to another department or another medical institution, the physician in charge of therapeutic at the transferring patient will listen to events, adverse events, and other necessary information as much as possible and enter this information into the EDC system.

1. Query correspondence

If the data center issues a query requiring checks, additions, or amendments to the EDC system input, the investigator or study collaborator shall confirm the EDC system data, then add and amend it accordingly, and submit the eCRF (transmit) after electronic signatures are signed by the investigator or sub-investigator. Data from sub-cohort studies will be handled as described in the respective sub-cohort study Appendix.

# Adverse event

## Definition of adverse events

### Adverse event

Adverse events are any unfavorable or unintended sign (including an abnormal laboratory finding), symptom, or disease that occurs during the observation period from the date of acquisition of consent, regardless of causal relationship with the drug, etc. Adverse events include those related to surgical stress.

### Serious Adverse Events

A serious adverse event is any of the following:

1. Death
2. May result in death
3. Requires hospitalization in a hospital or clinic or prolongation of hospitalization for therapeutic
4. Disorder
5. May lead to disability
6. Other serious cases according to 1 to 5
7. Any congenital disease or anomaly in the offspring of a treated patient.

## Investigation Items and Collection Procedures for Adverse Events

### Check items of adverse events

When the investigator or sub-investigator confirms the occurrence of an adverse event, the following items will be investigated.

1. Name of adverse event
2. Day of onset
3. Seriousness

- Serious or non-serious
- Severity level

Serious adverse events were defined as "10.1.2.Serious Adverse Events".10.1.2

1. Outcome, date of confirmation of outcome

Outcome and confirmation date of each adverse event will be collected.

- Outcome

Outcomes will be either "recovered," "improved," "recovered but with sequelae (and sequelae)," "not recovered," "died of the event," or "unknown" (and reasons)"

- Date of confirming outcome

When the outcome is "recovered" the day of resolution, when the event is "improved," "recovered but with sequelae," "not recovered" or "unknown" the date of confirmation of outcome, and when the event is "died" the date of death.

1. Presence or absence of causally related drugs

- Name of drug related

The judgment of causality with the drug shall be based on the following criteria.

[Causality]

When there is a reasonable temporal correlation between the occurrence of an adverse event and the administration of the drug, and it is not appropriate to judge it to be due to the condition of the subject or a factor other than the drug concerned (primary disease, complication, concomitant drug, etc.), and the relationship to the drug concerned cannot be denied.

Not related

When there is no reasonable temporal correlation between the occurrence of an adverse event and the administration of the drug, or when it is reasonable to judge that the occurrence of an adverse event is due to the status of the subject or to factors other than the relevant drug (primary disease, complications, concomitant drugs, etc.), and the relevance of the drug can be denied.

If Ricciana is administered within one week before the onset of the adverse event, or if the drug concerned is a product approved for marketing by Daiichi Sankyo Company, Limited or a product marketed by another company, the following items should be investigated.

1. Procedure

- Administration of anticoagulants (continued (no dose reduction), "decreased dose," "withdrawal/discontinue of administration," or "developed after completion of administration")
- Presence or absence of other treatment

If any, describe details such as drug treatment.

1. Other Possible Factors

- Presence or absence of other possible factors

　　If any, describe the details.

1. Details of the status of administration of the drug related to the drug (if the drug related to the drug is "Yes")

- Drug name
- Daily dose
- Treatment period

In addition, in the case of a product of Daiichi Sankyo Company, Limited that has been treated with Ricciana within one week before the onset of the adverse event, or a drug related to the event, and in the case of a serious adverse event, the following items will be examined in addition to the above.

- Details of concomitant medications used in the event of an adverse event: name, daily dose, and duration of treatment
- Related laboratory values at the time of onset of adverse events: name, date, and laboratory values
- Clinical course

### Procedures for Response in the Event of an Adverse Event

If an adverse event occurs, the investigator or sub-investigator shall explain the event to the study population and take necessary measures. In addition, research collaborators, including the principal investigators, will investigate the items required for adverse events (see 10.2.1 "Investigation items of Adverse Events") and promptly enter the investigation results and interpretation results into the EDC. The principal investigator, etc. will determine the causal relationship with the drug.10.2.1

## Responding to Serious Adverse Event

Within this study, only subcohort study A will perform the examination with minor invasion, so the correspondence to serious adverse events described in this section will only apply to subcohort study A.

### Response of study collaborators, etc.

When the research collaborators, etc. are aware of the occurrence of serious adverse events arising from blood sampling conducted in Sub-Cohort Study A during the course of this clinical study, they shall explain the information to the research subjects, etc. and take necessary measures in accordance with the procedure manual prepared by the head of the research institution. Research collaborators should promptly report the event to the principal investigator.

### Response by investigators, etc.

If the investigator or sub-cohort study A becomes aware of the occurrence of serious adverse events arising from blood sampling during the course of this clinical study, the investigator or sub-investigator will promptly report this to the head of the study site and take appropriate measures in accordance with the procedures prepared by the head of the study site.

The investigator or sub-investigator should promptly report the adverse event to the Study Secretariat (or enter it into the EDC system). Subsequently, the Research Secretariat, which has received reports from the principal investigators, etc., shall promptly share information on the occurrence of such adverse events with research collaborators, etc. involved in this subcohort study and investigators of other participating medical institutions.

(Cooperation with the Study Sponsor)

If adverse reactions related to a drug are observed during the course of this clinical study, the investigator or sub-investigator shall report the event to the pharmaceutical company that manufactures and markets the drug and cooperate with the post-marketing safety measures. Adverse reactions for which reporting is required by the Law Concerning the Assurance of Quality, Efficacy, and Safety of Drugs, Medical Devices, etc., of products sold by Daiichi Sankyo Company Limited shall be reported to the Pharmaceuticals and Medical Devices Agency by Daiichi Sankyo Company, Limited. The study subjects reported are posted as "Information on Case Reports Suspected for Adverse Drug Reactions" on the website of the Pharmaceuticals and Medical Devices Agency (http://www.pmda.go.jp/ [(Link)](http://www.pmda.go.jp/)). In such cases, the source of the report and the privacy of the study subject are regarded as unpublished.

### Response of the head of the study site

The head of the study site participating in Sub-Cohort Study A prepares a procedure manual on the matters to be implemented by the investigators etc. in the event of a serious adverse event arising from blood sampling conducted in Sub-Cohort Study A in advance, and takes necessary measures to ensure that appropriate and smooth responses are taken in accordance with the procedure manual. If the investigator or sub-cohort study A reports the occurrence of serious adverse events resulting from blood sampling, the investigator or sub-cohort study A will promptly take necessary actions in accordance with the documented procedure and seek the ethics review committee's opinion on the relevant adverse events and take necessary measures.

# Observations

The principal investigators and research collaborators will investigate the following items in accordance with "12. Survey Schedule" for all enrolled research subjects, enter them in the EDC system Case Study Form, and submit (transmit) the eCRF by electronic signatures of the investigators etc.12

## Enrollment survey

1. Patient identifying information

- Patient Registration Identification Number (excl Patient Chart Number)
- Sex
- Date of birth or age at the time of informed consent
- Date of consent

If the following test items are measured in the daily medical care, they are entered in the eCRF.

- - PT-INR level and date of measurement
    (Enter up to 6 values measured in the first half year of enrollment [1-month interval as a guide].)

1. Clinical course and laboratory values

If the following test items are measured in the daily medical care, they are entered in the eCRF.

- - Office blood pressure

Systolic and diastolic blood pressures will be measured (see Table 3 for measurement methods)Table 33

- - Hemoglobin
  - Serum creatinine
  - HbA1c

Table 33 Office blood pressure measurement

| 1. Device | a. Auscultation by mercury sphygmomanometer and aneroid sphygmomanometer with precision test is used. Accuracy-calibrated digital blood pressure monitors are also ^1^ to be used  b. Cuffs 13 cm in width and 22-24 cm in length of the internal cuff rubber sac are used  [Pediatric cuff for children < 27 cm and large cuff for adults for large arms (> 34 cm arm circumference)]. |
| --- | --- |
| 2. Measurement conditions | a. Quiet, suitable room-temperature environment  b. After a few minutes of rest in a backrest chair with the feet set first  c. Don't know the conversation  d. Do not smoke, drink alcohol, or consume caffeine before measurement |
| 3. Assay | a. Cuff position is maintained at heart height  b. Rapidly pressurize the cuff  c. Cuff exhaust rate is 2 to 3 mmHg per beat or sec  d. In auscultation method, the start of Korotkoff phase I is made to be a systolic blood pressure, and phase V is made to be a diastolic blood pressure. |
| 4. Number of the measurements | At least two measurements at 1-to 2-minute intervals. If the two measurements differ greatly, perform additional measurements. |
| 5. Determination | a. The mean of two stable values of ^2^ is taken as the blood pressure value.  b. Diagnosis of hypertension is based on BP levels at least on 2 or more different occasions |
| 6. Other precautions | a. Blood pressure difference between the right and left brachials was confirmed at the initial examination.  b. Do not wrap cuffs on thick shirts or overwear. Do not put thick shirts on the upper arm.  c. In cases of orthostatic hypotension, such as diabetes mellitus and the elderly, blood pressure should be measured 1 minute and 3 minutes after standing to check for orthostatic hypotension.  d. The auscultator should be a person with sufficient hearing and sufficient guidance for measurement.  e. Pulse rate must be measured and recorded |

1. Recently, the use of the electronic sphygmomanometer is advised from environmental effects of mercury, quality control of the mercury column, issues of the accuracy of the aneroid sphygmomanometer, etc.. Hybrid sphygmomanometers using electronic analog pillars instead of mercury meters are also available. Large errors arise when automatically wrapped blood pressure monitors are used in waiting rooms, etc. if they are not measured under sufficient guidance and management.

2. A stable value is an approximate value where the difference in the measured value is less than about the 5 mmHg as a guide.

Reference Source: Hypertension Treatment Guidelines 2014, p.16

## 12-month and 24-month surveys (permissible range: within 1 year after the date of obtaining informed consent, and within ±60 days 2 years after the date of obtaining informed consent)

1. Patient identifying information

- Patient Registration Identification Number (excl Patient Chart Number)

1. Confirmation of the status of continuation of consent
   - Whether consent was withdrawn or not, date on which consent was withdrawn
2. Checking visit status and health status
   - Confirmation of health (date of confirmation, method of confirmation, results of confirmation)
3. Administration of anticoagulants
   - Presence or absence of anticoagulant treatment at the start of the observation period
   - Type of anticoagulant at the start of the observation period
   - Daily anticoagulant dose and number of daily doses (DOAC only) at the beginning of the run-in period
   - Starting day of anticoagulant therapy
   - Date of completion of anticoagulation
   - Reason for change or discontinue of administration
4. Investigation of concomitant medications and therapies other than anticoagulants
   - At the end of each observation period, the use of the following drugs will be investigated

Antiplatelet drugs, p-gp inhibitors

- - The maximum number of oral medications used during the observation period (all medications including anticoagulants and antiplatelet agents, except topical and over-the-counter medications)

1. Status of non-pharmacologic therapy for AF

- Presence or absence of non-pharmacological treatment during the study period
  - If yes, the date of implementation, status of administration of antiplatelet drugs before and after surgery, and presence or absence of heparin bridges.

1. Implementation status of invasive procedures other than AF treatment (including minor surgery*)
   - ^[[1]](#footnote-1)^Presence/absence of invasive procedures (including minor operations*) other than NVAF therapeutic during the study period**^エラー! ブックマークが定義されていません。^**

If yes, date of implementation, type of invasive surgery (major surgery, minor surgery*), status of administration of antiplatelet drugs before and after surgery, and presence or absence of heparin bridges.**^エラー! ブックマークが定義されていません。^**

1. Blood clotting tests (only in patients taking warfarin)

If the following test items are measured in the daily medical care, they are entered in the eCRF.

- - PT-INR values, dates of measurements
    (Maximum six measured values during the observation period (based on two-month intervals).)

1. Clinical course and laboratory values

If the following test items are measured in the daily medical care, they are entered in the eCRF.

- - Body weight
  - Office blood pressure (systolic and diastolic; see Table 3 for measurement methods)
  - Pulse rate
  - Hemoglobin
  - Serum creatinine
  - HbA1c

1. Cardiovascular events

For events (1) to (8) below, the name of the event, details of the event, PT-INR level immediately before the event, presence or absence of administration of antiplatelet drug immediately before the event, type of oral drug immediately before the event, number of types of oral drug immediately before the event, seriousness, treatment, other measures, outcome, and date of outcome (if the outcome is "death" the date of death), causally related drugs, factors other than the drug, and comments on the adverse event will be investigated.

1. Stroke (including transient ischemic attack)

Details of events: type of stroke (atherogenic, cardiogenic, lacunar, haemorrhagic, unclassifiable, other stroke, TIA), presence of neurological symptoms, presence of imaging, Japanese version of modified Rankin Scale (mRS), National Institutes of Health Stroke Scale(NIHSS), acute-phase treatment processes, and acute-phase outcomes

1. Systemic embolism

Details of events: presence or absence of imaging

1. Intracranial haemorrhages other than haemorrhagic stroke (including subarachnoid haemorrhage, subdural/epidural haemorrhage)

Details of events: type of intracranial hemorrhage (subarachnoid hemorrhage, subdural/epidural hemorrhage, other), presence of neurological symptoms, presence of imaging, acute treatment process, and acute-phase outcome

1. Cardiac sudden death
2. Myocardial infarction

Details of events: clinical presentation, rationale for diagnosis, presence of cardiac intervention, and type

1. Cardiac intervention other than myocardial infarction

Details of events: primary disease name, type of cardiac intervention

1. Heart failure requiring hospitalization

Details of Events: Clinical Presentation

1. ① Deaths other than (7)

Details of events: Cause of death type (cardiovascular death, non-cardiovascular death, unknown), cause of death

1. Gastrointestinal bleeding

Site (name of adverse event), presence or absence of ulcer/reflux esophagitis, bleeding classification (Table 4), shock index, treatment, presence or absence of pylori, treatment, hemoglobin level before and after bleeding, PT-INR level immediately before the event, presence or absence of antiplatelet therapy immediately before the event, type of antiplatelet therapy immediately before the event, presence or absence of PPI therapy immediately before the event, number of oral medication immediately before the event, seriousness, procedure, other procedures, outcome, date of outcome, drugs with causal relationship, comments on adverse events, possible factors other than the drug, and adverse events.Table 44

1. Other Haemorrhagic Adverse Events (Other than Hemorrhagic Stroke, Intracranial Hemorrhage, and Gastrointestinal Bleeding)

Adverse event name, bleeding class (Table 4), date of onset, PT-INR level immediately before the event, type, type of oral drug immediately before the event, type of oral drug immediately before the event, seriousness, procedure, other procedure, outcome, date of outcome, drug causally related, drug other possible factors, comments on adverse events

Table 44 Definition of Bleeding Grouping

| Haemorrhage Grouping ^1^ | Definition |
| --- | --- |
| Major bleeding (Major bleeding) | Clinically evident bleeding (bleeding visually evident by examination or radiologic imaging) that meets at least one of the following  ・ Fatal loss of blood  ・ Symptomatic intramuscular hemorrhage with retroperitoneal, intracranial, intraocular, intrathecal, intraarticular, pericardial, or compartment syndrome  ・ Clinically evident haemorrhage ^※^ with a decrease in haemoglobin of 2.0 g/dL or more requiring transfusions  When 2 units (400 cc) of ^※^ concentrated red blood cells or whole blood are transfused, it is converted to hemoglobin reduction of 1.0 g/dL. Haemorrhage associated with a surgical procedure is defined as bleeding that is greater than the amount of bleeding observed during routine operation or procedure. If no hemoglobin data are available, the hematocrit level is reduced by at least 6.0% and bleeding requiring blood transfusion is considered. |
| Clinically relevant bleeding (Clinically relevant non-major bleeding) | Clinically evident bleeding requiring treatment. Examples include, but are not limited to, diagnostic tests and treatments listed below. Outpatient visits without any of the following or similar medical procedures (diagnostic tests and treatments) do not fall under "require treatment."  ・ Inpatient hospitalization or prolongation of existing hospitalization  ・ Laboratory tests  ・ Imaging test  ・ Endoscopy; colonoscopy; cystoscopy; bronchoscopy  ・ Nasal packing  ・ Compression tourniquet  ・ Ultrasound-guided aneurysm closure  ・ Coil embolization  ・ Inotropic support  ・ Surgery  ・ discontinue or discontinuation of anticoagulant therapy as directed by the physician  ・ Change of concomitant treatment other than anticoagulants (reduction or discontinue of aspirin, etc.) as directed by the physician |
| Minor bleeding [Minor (not clinically relevant) bleeding] | Other obvious bleeding that does not meet the criteria for major bleeding or clinically important bleeding (e.g., epistaxis without treatment). |

1 Modified definitions of phase III, MNCT ^2525^

1. Other events

Presence or absence of falls and fractures (extrinsic or intrinsic)

If yes,

Name of the adverse event, date of onset, PT-INR immediately before the event, presence or absence of antiplatelet therapy immediately before the event, type, seriousness, procedure, other procedure, outcome, date of outcome, drug(s) related to the event, drug(s) possibly related to the event, comments about the adverse event(s)

1. Other adverse events

If a serious adverse event occurs or if Licciana is administered within one week before the onset of the adverse event, the following items will be investigated.

Name of adverse event, date of onset, seriousness, procedure, other procedure, outcome, date of outcome, drug(s) of causal relationship, drug(s) other possible cause(s), adverse event(s)

(10) For (14), the study subject will be contacted by telephone or letter even if there is no visit, and the event status will be checked at 12 and 24 months.

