## Secondary endpoint

Occurrence of the following events during the observation period

1. Hemorrhagic Adverse Events (Major Bleeding)
2. Stroke
3. Systemic embolism
4. Ischemic stroke
5. Hemorrhagic stroke
6. Intracranial hemorrhage
7. Cardiovascular events (stroke, myocardial infarction, non-myocardial infarction cardiac intervention, heart failure requiring hospitalization)
8. Death due to cardiovascular disease (death due to cardiovascular causes undeniable)
9. All deaths

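### Table 4 makes transfusion a condition of the hemoglobin criterion for major bleeding while its own note treats transfusion as a correction, so class can follow transfusion practice instead of bleed size

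*Protocol*

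**What the plan says.** Table 4 in protocol section 11.3 (12-month and 24-month surveys) defines major bleeding as clinically evident bleeding "that meets at least one of the following". There are three criteria: fatal bleeding; bleeding at a listed critical site or with compartment syndrome; and bleeding "with a decrease in haemoglobin of 2.0 g/dL or more requiring transfusions".

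A reference mark ties the third criterion to a note in the same cell. The note says that when 2 units (400 cc) of "concentrated red blood cells or whole blood are transfused, it is converted to hemoglobin reduction of 1.0 g/dL". For cases without hemoglobin data it gives a fallback: "the hematocrit level is reduced by at least 6.0% and bleeding requiring blood transfusion is considered".

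The next class, clinically relevant non-major bleeding, is "Clinically evident bleeding requiring treatment", and anything left over is minor. The table's footnote gives its origin as "Modified definitions of phase III, MNCT" and does not explain what was modified.

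Major bleeding is the first item under Secondary endpoint in section 15. It is also a follow-up analysis item in section 17.3 and a named outcome in the analysis of sub-cohort A (section 17.5.1).

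In section 11.3, the items for gastrointestinal bleeding include hemoglobin before and after the bleed. The items for other haemorrhagic adverse events include the Table 4 class but no hemoglobin values. Neither list names units transfused.

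**The concern.** The criterion and its note use transfusion in two different ways. The note adds transfused blood back to the measured fall, so that a bleed partly masked by transfusion is judged by its true size. The criterion instead admits a bleed only if it required transfusion, whatever its size. With both in force, a larger bleed can fall in a lower class than a smaller one.

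This matters because the study is observational, does not direct treatment, and plans about 1,000 sites. An endpoint that turns on whether a patient was transfused will vary with each site's habits. The study aims to define the population best suited to DOAC treatment, and major bleeding is on the harm side of that judgment.

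**Working it through.** **Inputs, all from Table 4.**
- Threshold: fall of 2.0 g/dL or more.
- Condition in the same criterion: transfusion required.
- Conversion: 2 units = 1.0 g/dL, that is 0.5 g/dL per unit.
- Fallback: hematocrit fall of at least 6.0% and transfusion required.

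The protocol gives no rate, power or sample size for major bleeding, so there is no stated figure to reproduce. The check applies the rule to cases.

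**Formulas.** Adjusted fall = measured fall + 1.0 g/dL × (units ÷ 2).
- Rule as written: adjusted fall ≥ 2.0 g/dL and transfused.
- Transfusion as a correction only: adjusted fall ≥ 2.0 g/dL, transfused or not.

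**Cases (non-fatal, outside the listed sites).**

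| Measured fall (g/dL) | Units | Adjusted fall (g/dL) | As written | Correction only |
|---|---|---|---|---|
| 2.0 | 0 | 2.0 | not major | major |
| 3.5 | 0 | 3.5 | not major | major |
| 5.0 | 0 | 5.0 | not major | major |
| 1.0 | 2 | 1.0 + 1.0 = 2.0 | major | major |
| 0 | 4 | 0 + 2.0 = 2.0 | major | major |
| 1.5 | 2 | 1.5 + 1.0 = 2.5 | major | major |
| 0.9 | 2 | 0.9 + 1.0 = 1.9 | not major | not major |

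As written, every untransfused bleed in the table is non-major, and the 5.0 g/dL bleed ranks below one worth 2.0 g/dL. Under the correction-only rule the class follows the adjusted fall throughout.

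**Does this depend on the conversion?** No. If the note is ignored and the rule is measured fall ≥ 2.0 g/dL and transfused, a transfused 2.0 g/dL fall is major and an untransfused 5.0 g/dL fall is still not.

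**Size.** Among non-fatal bleeds outside the listed sites, let U be untransfused bleeds with a fall of 2.0 g/dL or more, and T transfused bleeds with an adjusted fall of 2.0 g/dL or more. Let C be the fatal and critical-site bleeds.
- Share of hemoglobin-criterion bleeds missed: U ÷ (U + T).
- Share of all major bleeds missed: U ÷ (U + T + C), which is smaller whenever C > 0.

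The protocol gives none of U, T or C. Any percentage put here would only restate an assumed untransfused share. Only the direction follows: fewer bleeds counted as major.

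**The case against.** The strongest objection is that this is a translation slip. The English is rough throughout, the critical-site criterion in the same cell is garbled, and the conversion note fits an intended meaning of a fall corrected for transfusion. That may well be so. But the condition appears twice, for hemoglobin and for hematocrit, and nothing elsewhere in the protocol corrects it. A site or committee following the text would misclassify, so the wording needs reconciling either way.

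A second objection is that the condition is a deliberate marker of severity, since the footnote calls the definitions modified. The documents neither confirm nor exclude this. If it is deliberate, it should be stated.

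On verification, a reader might infer that the criterion cannot be checked at all outside the gastrointestinal tract. That goes too far. Sites record the Table 4 class, the Event Evaluation Committee (section 27.6) judges bleeding events, and queries and source verification are provided for. Section 10.2.1 also collects related laboratory values for some serious events linked to the sponsor's products. What stands is narrower: the bleed-specific item list for other bleeds has no hemoglobin values from which the committee could verify this criterion.

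A reader might also infer that the problem reaches every sub-cohort with a bleeding outcome. Four sub-cohorts (A, D, F and G) list hemorrhagic adverse events, but only the analysis of A names major bleeding. D, F and G analyse bleeding events without restricting them to major, so movement between classes need not change their results.

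Finally, the affected bleeds are not lost. Section 17.3 analyses clinically relevant and minor bleeding as separate items.

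**Conclusion.** The point holds for non-fatal bleeds outside the listed critical sites and without compartment syndrome. For these, Table 4 as written excludes any untransfused hemoglobin fall from major bleeding, however large, and admits a 1.0 g/dL fall with 2 units. The first secondary endpoint and the major-bleeding analysis in sub-cohort A therefore depend partly on local transfusion practice.

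The bias is toward fewer major bleeds. A reader might want a percentage under-count, but the protocol does not support one, because it gives neither a major-bleeding rate nor the share of such bleeds that are transfused.

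The conclusion takes the text at its word and treats a bleed that required transfusion as one that was transfused. A bleed judged to need transfusion but not transfused has no clear class, which is a further ambiguity.

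The primary endpoint is unaffected. So is the sample-size rationale, which rests on stroke/systemic embolism and intracranial hemorrhage; intracranial bleeding is major by site, whatever the hemoglobin fall.

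**What to change.** Reconcile the hemoglobin criterion, the hematocrit sentence and the conversion note in Table 4, in one of two ways:

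1. Make transfusion a correction: a fall of 2.0 g/dL or more after adding 1.0 g/dL for every 2 units (400 cc) transfused, whether or not blood was given. Remove the transfusion condition from the 6.0% hematocrit fallback too, and say how transfused units are handled there, since the note converts only to hemoglobin.
2. If the condition is deliberate, say so, state whether it means transfusion required or transfusion given, and report a sensitivity analysis of major bleeding without it.

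Under either option, add units transfused to the eCRF for all bleeds, including gastrointestinal ones, and hemoglobin before and after the bleed for non-gastrointestinal bleeds. Without these items neither the corrected fall nor the sensitivity analysis can be computed from the listed data.

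The cost is one table edit and a few eCRF fields. The change concerns how events are classified and has no bearing on when a patient should be transfused.
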